#### Data analysis

We will use the Framework approach^16^ to analyse the data in five stages: (1) familiarisation with the data, (2) identifying the thematic framework, (3) indexing, (4) charting, and (5) mapping and interpreting. This process enables the researcher to identify emerging themes or issues in the data. Little is known about why NHS Trusts choose to deliver specific OPAT models. Evidence generated from the literature review and input from our clinical co-applicants will be used to refine the thematic framework. The thematic analysis will be modified in the light of new data, and a process of constant comparison will be used to examine across themes and cases. The findings from the interviews will inform the modelling and DCE work streams and will be considered by the expert panel.

### Cost-effectiveness

This work package will provide an economic model of the different delivery systems to evaluate their cost-effectiveness in both short-term and longer term infection patients groups.

A decision-analytic model will be developed to estimate the cost-effectiveness of OPAT services. Published best practice modelling guidelines will be applied.^17^ The analysis will conform to the reference case set out by the National Institute for Health and Care Excellence (NICE)^18^ using a cost-utility analysis (CUA) between service models and effectiveness measured by QALYs. It is possible that the relative benefits of the service models may not register in terms of QALY gains (especially for short-term infections where treatment may last less than 1 week). Therefore, we will also conduct a cost-effectiveness analysis based on cost per patient successfully treated. We will take the perspectives of the healthcare provider and personal social services and of the patient/carer in separate analyses. Daily hospital treatment service will be considered ‘standard care’ for the analysis. The model structure will be informed by previous models in the area and through discussions with clinicians and patients.

We will adhere to NICE technology appraisal guidelines and subsequent Technical Support Documents produced by the NICE Decision Support Unit in identifying and selecting parameters.^19^ Data (eg, NHS resource use and costs, service model efficacy, event and risk probabilities and utility values) for the economic model will be derived from the literature review, from the DCE interviews, from retrospective retrieval of hospital and general practitioner records and from clinical experts. Patients’ use of NHS resources will be captured indirectly from medical records and directly from patient reports of service use by those participating in the DCE. Research nurses will extract data (with patient consent) on treatments received, effectiveness, duration and location, treatment delivery systems, additional health services used or visits required and adverse events. We aim to extract a minimum of 400 records across short-term and long-term infection patients and across services (ie, n=50 per infection type per service model). All data will be anonymised. If we have insufficient data on particular parameters, we may convene a clinical expert and patient consensus panel to agree on suitable model values.

Unit costs for treatments, health service staff and resources will be obtained from the Personal Social Services Research Unit (PSSRU), the British National Formulary (BNF) and NHS Reference cost database. Health state utility values for the CUA will be obtained from those participating in the DCE completing an EQ-5D^20^ questionnaire, which is NICE's preferred source of utility values. The EQ-5D is a simple, five-item questionnaire which provides utility values based on a UK general population-derived tariff.

#### Data analysis

The CUA will compare the three models of community intravenous antibiotic service delivery to daily hospital attendance (considered ‘standard care’). The Markov decision model will be developed to describe the patient pathway and potential outcomes and provide estimations of expected costs and benefits for the service models. The results will be presented as expected incremental cost-effectiveness ratio, expected net benefit (assuming λ is equal to the NICE QALY threshold of £20 000) and a cost-effectiveness acceptability curve.^21^ QALYs will be based on EQ-5D utility values although estimates for other health states that may be required in the model (eg, for hospitalisation or hospital-acquired infections) may come from direct values found in the literature.

Deterministic one-way, multiway and scenario sensitivity analyses will explore the sensitivity of the results to the modelling assumptions and parameter values selected. Probabilistic sensitivity analysis via Monte Carlo simulations will be undertaken to test the robustness of the results to parameter uncertainty. We will use the value of information framework to explicitly quantify the implications of decision uncertainty. We will calculate the expected value of perfect information^22^ to help determine the value of, and priorities for, future research and the expected value of sample information to design efficient future research. Recently proposed regression methods for achieving this will be employed.^23^ This information will be used by the team and clinical trial statisticians to plan any future clinical trials.

### Discrete choice experiment

This work package will determine patient preferences for different community intravenous antibiotic service attributes through the use of a DCE.

The quantitative study of patient preference choices involves the use of discrete choice models, which are mathematical structures belonging to the family of random utility models (for a comprehensive review see Train^24^). A substantial number of studies in health economics now make use of choice modelling techniques^25^ and our methodology will follow best practice established in Lanscar and Louviere.^26^ Attribute development will be conducted in two phases using recommendations by Coast *et al*^27^ followed by the development and piloting of the DCE interview outlined by Willis.^28^ Information from the literature review and record retrieval (eg, on treatment effectiveness) will also inform survey content. Our patient advisory group (PAG) will be closely involved with this work package, providing input into the development of study materials (eg, DCE items) and interpretation of interview data. They will also provide a patient perspective on the interpretation of the resulting models.

#### Phase 1 (attribute development)

Design: We will undertake a qualitative exploration of patient's experiences of receiving intravenous antibiotic services and their views on the important aspects of the service. The use of primary qualitative data to inform the development of DCEs is relatively recent; therefore, we will follow guidance developed by Coast *et al*.^27^

Sample: Adults (n=30–50) who have experienced community intravenous antibiotic treatment will be purposively selected using a sampling matrix ensuring a range of intravenous antibiotic services, treatment lengths and diverse backgrounds are represented.

##### Data collection

Focus groups will be offered to participants to present their ideas and experiences, and to generate new ideas. To maximise recruitment, interviews will be offered to those unable/reluctant to attend a focus group. A topic guide will be developed from the literature to guide discussions, and all sessions will be facilitated by experienced researchers. All session will be recorded (with consent) and transcribed verbatim.

##### Data analysis

The principle approach will be content analysis, with data analysed for patterns and themes, to develop categories and subcategories of attributes to generate a comprehensive set of attributes. Data will be analysed iteratively using constant comparative methods^29^ involving close reading of the data to identify words that capture thoughts or concepts. The results of the analysis will be used to construct the attributes and levels for the DCE scenarios.

#### Phase 2 (refinement of terms)

After further refinement, we will pilot the DCE using a ‘think aloud’ cognitive interviewing technique^28^ with a ‘naive’ sample of participants (n=30) to test understanding and identify problems.

#### Phase 3 DCE

Sample: Participants will be recruited from the sites providing each of the services under investigation (described above). Patients will be eligible if they are currently receiving intravenous antibiotics in the community, as an outpatient, or have previously received such a course of intravenous antibiotics within the past 24 months (identified retrospectively from records).

##### Sample size

The sample sizes for DCEs depend on the number of choice tasks completed by respondents and the number of attributes and levels presented in each choice. As the first stage of the study is the development of the DCE, we have used estimates from previous work which would suggest that 200 participants with short-term and longer term infections should be sufficient to allow determination of robust preference data.^30^ We will use advanced survey design techniques that maximise the potential for trading between attributes to enhance the data quality.^31^

##### Data collection

The interviews will be carried out by the researcher using a laptop to present the choices to respondents on a one-to-one basis.

##### DCE questionnaire

We envisage presenting each respondent with 8–10 different choice scenarios. The planned pilot survey will allow us to determine the most appropriate survey design.

##### Data analysis

Data will be analysed using advanced mixture models allowing us to accommodate the expected high level of heterogeneity in sensitivities/preferences across individual patients.^32^ We will seek to explain this heterogeneity by linking sensitivities to patient characteristics, and the use of constructs that allow us to explicitly incorporate underlying attitudes.^33^ Any remaining unexplained heterogeneity will be accommodated in a random manner. Hess *et al*^34^
^35^ have shown that an appropriate approach to the various types of heterogeneity is likely to provide more robust overall measures of sensitivities. The attitudinal data will also mitigate the effects of any strategic bias that may arise in the data.

### Expert panel

The final work package comprises an expert panel to agree on what may constitute the optimal service model(s) of community intravenous antibiotics delivery and how future clinical trials should be designed to test these services.

The expert panel will consider the evidence generated from the literature review, economic modelling, DCE and survey of current service provision. A consensus will be sought on what is likely to represent optimal community intravenous antibiotic therapy for the two patient groups (long-term and short-term intravenous antibiotic patients). Membership of the panel will consist of 2–4 service user representatives (including members of our PAG) together with healthcare staff currently involved in intravenous antibiotic delivery, pharmacists, GPs, NHS commissioners, health economists and a clinical trials statistician.

#### Data collection and analysis

The expert panel will consider which service delivery models and which particular configuration of these models warrant full evaluation in a clinical trial. The panel will consider the design of future clinical trials, identifying ways to overcome potential barriers to service provision and formulate a plan of future research priorities.

The proposed research will address significant gaps in knowledge about the clinical and cost-effectiveness of different intravenous antibiotic services; identify which services patients prefer and which aspects of the services are most important to them. Since the services available to patients are likely to have different costs, effects and risks, it is essential to understand what patients consider most important in the care they receive and what trade-offs they are willing to make. The optimal delivery of OPAT may mean offering patients a choice between several services concurrently which has consequences for future planning and resourcing. The panel will be asked to consider these options.

### Consent

Patients with experience of community intravenous antibiotic treatment will be approached by the research nurses either while they are still under the care of the hospital or retrospectively when then have completed treatment. All eligible patients will be given a patient information leaflet to consider and if they are willing to participate they will be consented and registered.

### Confidentiality

Monitoring and extraction of data from patient records will be carried out by the research nurses with the full consent of the patient and anonymised. Data will be handled in accordance with the 1998 Data Protection Act at all times. Patients and staff members who consent to be interviewed or to participate in focus groups will be assured of the confidentiality and secure handling of the recordings and transcripts.

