#### Criteria for selection of studies

Studies will be eligible for inclusion if the participants are individuals or groups of adult patients or care providers *and* they evaluate the clinical effectiveness or cost-effectiveness of an OPAT model, *or* they describe or evaluate patient safety issues associated with OPAT, *or* they consider the acceptability of OPAT from the perspective of the patient receiving treatment or the practitioner delivering care. Any form of intravenous delivery system will be included (eg, infusion or bolus).

Studies will be excluded if they make reference to clinical effectiveness but do not report on specific patient outcomes. Similarly, studies that consider costs related to a model of delivery without considering patient benefit alongside these, and studies making reference to costs and benefits without reporting specific cost-effectiveness data (eg, cost per quality-adjusted life year (QALY)) will also be excluded. Studies that include children will be reviewed but excluded if they do not report outcomes for adult patients separately. Studies involving multiple routes of delivery of antibiotics will be reviewed but will be excluded if they do not report outcomes for patients receiving intravenous treatment separately.

The outcomes of interest are clinical effectiveness (cure or improvement, duration of treatment), cost-effectiveness (cost, benefit), safety (complications, adverse events, hospital admission), patient acceptability and provider acceptability.

Both experimental (randomised controlled trials, controlled clinical trials, controlled before and after studies) and non-experimental (case–control, cohort, cross-sectional, other observational) studies will be included. Quantitative, qualitative and mixed-methodology studies will be included.

The review and synthesis of data will be undertaken in accordance with the Centre for Reviews and Dissemination guidelines for systematic reviews.^12^ A protocol of the review was produced and added to the PROSPERO database (CRD ref: 4201300637 4).

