#### Evidence synthesis

The main characteristics of included studies and findings relating to clinical effectiveness, cost-effectiveness, patient safety and acceptability, and study quality will be summarised in narrative and tabular form. We anticipate that there will be substantial heterogeneity between included studies, and as such do not plan to pool data for meta-analysis. The synthesised review data will provide values for use in the economic model, DCE and evidence for consideration by the expert panel.

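### Record-based success and adverse-event estimates cover only patients able and willing to consent; those who die or lose capacity before being approached go uncounted, and no count of them is planned

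*Protocol article*

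**What the plan says.** Two places in the protocol article make record extraction depend on the patient's consent. The Cost-effectiveness section has "Research nurses will extract data (with patient consent", followed by a list that includes effectiveness and adverse events. The Confidentiality section has "Monitoring and extraction of data from patient records will be carried out by the research nurses with the full consent of the patient". Neither states an exception for patients who have died or cannot consent.

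The Consent section gives two points of approach: while the patient is still under hospital care, or after treatment has been completed.

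The records are one of several sources. The Cost-effectiveness section says that model inputs, among them "service model efficacy, event and risk probabilities and utility values", will be "derived from the literature review, from the DCE interviews, from retrospective retrieval of hospital and general practitioner records and from clinical experts". The Evidence synthesis section adds: "The synthesised review data will provide values for use in the economic model". Where data are insufficient, "we may convene a clinical expert and patient consensus panel to agree on suitable model values".

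The record target is at least 400, as 50 per infection type per service model. Alongside QALYs, the section plans an analysis of cost per successful treatment, because QALYs may not register differences for short infections.

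**The concern.** Entry to the record sample depends partly on the outcome being estimated. A patient who dies or loses capacity before approach contributes neither a failure nor a fatal adverse event, while a patient who recovers can be asked. If the missing patients did worse than those who consent, the record-based success probability is too high and the serious adverse-event probability too low.

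The cost-per-success analysis is the most exposed, since treatment success is its denominator. The longer-treatment group, for which the Design section gives bone infections as an example, is where death or incapacity before approach is most plausible.

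The sensitivity analyses do not remove the problem by themselves. Probabilistic analysis and the value-of-information calculations describe uncertainty around the estimates supplied; they do not shift a biased centre. One-way, multiway and scenario analyses could vary the failure rate, but without a count of unapproachable patients nothing indicates how far to vary it.

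**Working it through.** **The plan's own figure.** 50 records × 2 infection types × 4 service models = 400, which reproduces the stated minimum. The article gives no expected success, death or consent rate, so every rate below is an assumption.

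**General form.** Let *u* be the share of identified patients who could not be approached, S_obs the success among those observed, and s_u the success among the unapproachable. If those who are approached consent independently of outcome:

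- True success = (1 − u) × S_obs + u × s_u
- Overstatement = u × (S_obs − s_u)

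The overstatement is positive whenever the unapproachable did worse, and largest when s_u = 0, that is, when all of them count as failures.

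**Deaths only, s_u = 0.** With non-fatal failure f = 0.10 and death before approach d, true success is 1 − f − d and observed success is 1 − f/(1 − d).

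| d | True success | Observed success | Overstatement (points) |
|---|---|---|---|
| 0.01 | 0.890 | 0.899 | 0.9 |
| 0.02 | 0.880 | 0.898 | 1.8 |
| 0.05 | 0.850 | 0.895 | 4.5 |
| 0.10 | 0.800 | 0.889 | 8.9 |

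**Unequal willingness as well.** With f = 0.10 and d = 0.02, suppose patients with non-fatal failure consent at half the rate of successes. Observed failure is 0.05/(0.05 + 0.88) = 0.054, so observed success is 0.946 against a true 0.880, an overstatement of 6.6 points.

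**Between two services, f = 0.10 in both.**

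- Deaths 1% and 5%: true difference 0.890 − 0.850 = 4.0 points; observed difference 0.8990 − 0.8947 = 0.4 points.
- Deaths 3% and 3%: true and observed differences are both 0.

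So the contrast is distorted when the loss differs by service, and these equal losses leave it unchanged.

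**Scale against sampling error.** At n = 50 and 90% success, the 95% half-width is 1.96 × √(0.9 × 0.1/50) = 0.083, or 8.3 points. The bias at d = 0.01 or 0.02 is well inside this; at d = 0.10 it is slightly larger. More records shrink the sampling error but not the bias.

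**The case against.** The best case on the other side is that consented records are one of four named sources, and that the literature review already collects cure or improvement and "safety (complications, adverse events, hospital admission". Scenario analyses are planned, a consensus panel is available, and a journal article commonly leaves screening logs to the full protocol.

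Much of this stands, and it rules out four stronger readings that a reader might infer:

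- *That the model's success and event probabilities rest on the records alone.* The Cost-effectiveness and Evidence synthesis sections say otherwise.
- *That consent is sought up to 24 months after treatment.* The window "within the past 24 months (identified retrospectively from records" is an eligibility rule for the DCE and sits beside patients currently on treatment. Carrying it over to record extraction is plausible but not stated, and approach during care reduces the selection.
- *That all serious outcomes are lost.* A patient who was readmitted or had a serious event and later consents contributes that event. Only death or lasting incapacity before approach necessarily removes a patient.
- *That the loss differs between services.* The article says that services are likely to differ in effects and risks, which makes it plausible, but gives no mortality, case mix or consent rate by service.

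What does not stand is that the other sources settle the matter. DCE interviews also need living, consenting patients. The review expects substantial heterogeneity and no pooling, and its safety list does not name death. The Introduction says that the service types have had no robust comparison of cost-effectiveness. The records, with a target for each service and infection type, are the study's own service-specific data. Nor is this only an unreported detail: the consent condition is stated twice and fixes who can be counted.

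**Conclusion.** The point holds for the record-derived part of the model. Followed as written, the plan estimates success and adverse events among patients able and willing to consent, and overstates success if those lost before approach did worse. Under the assumed 10% non-fatal failure, with survivors consenting equally and every pre-approach death counted as a failure, the overstatement is about 1 to 9 points for death rates of 1% to 10%. It would be smaller if some of those lost had been treated successfully, and larger if living patients with failures consent less often.

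The actual size cannot be derived from the documents, nor can any distortion between services be shown to exist. How far the bias reaches the final results depends on the weight given to the records against the other sources. This is a worthwhile, inexpensive improvement; it does not invalidate the economic model.

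**What to change.** 1. Have research nurses log, by service model and infection type, the number of patients identified and the number who could not be approached because of death or incapacity.
2. Add to the planned scenario analyses one that counts these patients as treatment failures. Apply the logged share, as S_obs × (1 − u), and do not add the raw count to the consenting records. As an illustration, if 100 patients are identified, 5 are unapproachable and 50 consent, the share is 5/100 = 5%; adding 5 failures to 50 records would give them a weight of 5/55 = 9.1%.
3. Where Trusts can readily supply anonymised aggregate counts of deaths and readmissions among all OPAT starts, by service and infection type, use these or literature values for those parameters in preference to the consented records. Keep the consented records for resource use.

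The cost is an addition to the screening log, one extra model scenario and, if step 3 is taken up, a request to the seven Trusts. No individual record is extracted without consent. The log should start with recruitment, since it is harder to reconstruct later. The scenario is conservative, because some unapproachable patients may have been treated successfully, so it should be reported as a bound beside the base case.
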